### Data Management

Data will be collected with the secure Nettskjema platform and will be directly sent to and stored on a secure server that only members of the research team have access to. Data collection, data cleaning, and statistical analyses will also only be performed by members of the research team. The statistical analyses will be conducted on anonymized data from the secure server.

### Planned Statistical Analysis

Data analyses will be conducted using SPSS. Attrition analyses will be conducted to examine differences between those who complete the questionnaires and those who do not at different time points. A missing-values analysis will also be conducted. Variables for which there are a significantly greater number of missing values will be included as covariates in the analyses.

Correlations will be used to examine whether the different outcomes are related to each other at T1, and linear mixed models will be used to test the hypotheses. We will run 3-level mixed models with time nested within participants nested within schools, and model repeated measures using the *repeated* command in SPSS. We will assess the covariance structure of the repeated measurements by comparing models with different structures (ie, unstructured, compound symmetric, first-order auto-regressive, or others) using the Akaike information criterion.

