### Power Calculations

Power calculations were conducted with PASS 16 (NCSS, LLC). Using multilevel analysis with a significance level of .05 will require a total sample of 1250 adolescents (625 in both the intervention and control groups, including 25 schools with 25 students per school) to achieve a power of .79 and to detect a small effect corresponding to Cohen *d*=0.20 when the expected interclass correlation at the school level is 0.02. Anticipating a drop-out rate of approximately 25%, a total of 1563 adolescents should be recruited [15].

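### As worded, the missing-data rule picks covariates by how incomplete they are, not by whether they predict non-response or the outcome

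*Protocol article*

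**What the plan says.** Under Planned Statistical Analysis, the protocol article sets out three steps on missing data, in this order:

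- First comes a comparison of responders with non-responders: "Attrition analyses will be conducted to examine differences between those who complete the questionnaires and those who do not at different time points".
- Second, the article plans to look at the missing values themselves, without further description.
- Third, it fixes how covariates enter the models: "Variables for which there are a significantly greater number of missing values will be included as covariates in the analyses".

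The hypotheses are then tested with linear mixed models in SPSS: "We will run 3-level mixed models with time nested within participants nested within schools". The section does not say what the number of missing values is compared with, does not restrict the covariates to baseline, and does not say what happens to a record whose covariate value is missing. Under Power Calculations, the article expects substantial loss: "Anticipating a drop-out rate of approximately 25%, a total of 1563 adolescents should be recruited".

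**The concern.** A mixed model fitted by likelihood uses every observed outcome. It is valid if dropout is missing at random given the observed outcomes and the covariates in the model. An added covariate helps with dropout when it predicts who fails to respond and is also related to the outcome. The number of values that the covariate itself lacks shows neither of these things.

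Three consequences follow if an analyst applies the sentence as it stands:

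1. The covariates chosen have no necessary link to dropout, so the adjustment does not do the job for which it appears to be there.
2. A record without a value for a covariate cannot enter a model that conditions on that covariate unless the value is imputed. The rule favours exactly the variables for which this happens most often, so observed WHO-5 and SDQ scores can be lost.
3. Nothing limits the rule to T1. With attrition, T2 and T3 variables will tend to be the most incomplete. They are measured after schools are randomised and may be affected by the app.

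The rule governs the models that test the primary hypothesis, so it bears on both precision and bias of the main result.

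**Working it through.** **Step 1: criterion used against criterion needed.** The attrition analysis compares completers with non-completers. Its natural product is a list of T1 characteristics that predict non-response. The covariate sentence does not refer to that list. It refers to variables that have many missing values. The two sets may overlap, but only by coincidence.

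**Step 2: which variables qualify literally.** Under Secondary Outcomes, the app-specific questions at T2 and T3 go to the intervention group only, so every control lacks them. On the literal wording they would qualify, and conditioning on them would leave no controls. The T2 and T3 outcome scores would qualify too. The sentence therefore cannot be carried out as written without a restriction that it does not contain.

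**Step 3: the plan's own power figure.** Inputs from Power Calculations: 625 per arm, read as 25 schools of 25 students in each arm; d = 0.20; intraclass correlation 0.02; significance level .05, taken as two-sided.

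- Design effect = 1 + (25 − 1) × 0.02 = 1.48.
- Effective n per arm = 625 / 1.48 = 422.3.
- Power = Φ(d / √(2 / n_eff) − 1.96) = 0.828. With a t distribution on 48 degrees of freedom it is 0.813.

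The article states .79, so the figure is not reproduced exactly. The gap is small, on the conservative side, and does not affect this point. The formula is used below only to show how power moves.

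**Step 4: illustration of the loss.** Assumptions: 1563 × 0.75 = 1172 adolescents analysed; 25 schools per arm; a T1 covariate missing for a share p, spread evenly over schools; no imputation. The article gives no value for p, so a range is shown. With m = N / 50 students per school, n_eff per arm = 25m / (1 + (m − 1) × 0.02).

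| Assumed share missing | N analysed | m | n_eff per arm | Power |
|---|---|---|---|---|
| 0% | 1172 | 23.44 | 404.5 | 0.812 |
| 10% | 1055 | 21.10 | 376.2 | 0.783 |
| 20% | 938 | 18.76 | 346.1 | 0.749 |
| 30% | 820 | 16.40 | 313.5 | 0.707 |

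Starting from 1250 instead, with t on 48 degrees of freedom, power goes from 0.813 to 0.785, 0.751 and 0.710. The pattern is the same.

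**Step 5: does the rule reduce dropout bias?** A simulation with no true effect took 40,000 participants in two arms, with dropout depending on a baseline variable X in one arm only. The T2 outcome was regressed on arm and T1 outcome, with and without a further covariate. Two runs gave:

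| Added covariate | Estimated effect (truth 0) | Analysed |
|---|---|---|
| None | −0.051, −0.060 | 30,341; 30,323 |
| Unrelated variable, 20% missing | −0.047, −0.061 | 24,183; 24,355 |
| X, the predictor of dropout | +0.006, −0.003 | 30,341; 30,323 |

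The incomplete covariate cost about a fifth of the sample and left the bias where it was. The predictor of dropout removed it at no cost. This scenario is assumed, and nothing in the article says that dropout will behave this way. It shows only which property of a covariate matters.

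**The case against.** The best defence is the context. The sentence comes straight after the attrition and missing-values analyses, and its reference to significance suggests a comparison between groups. It may be a compressed way of saying that the models will adjust for characteristics associated with missingness. That is probably what was meant, and it would be sensible. The odd results of the literal reading in Step 2 also point to a slip in wording. This stands as a reading of intent, but the published text does not say it.

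The defence also limits the harm in ways that stand:

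- A reader might infer that the rule forces records to be discarded. It does so only if covariates are not imputed. The article does not say, and such detail is often left to an analysis plan.
- A reader might infer that the rule picks the opposite of the right variables, or leaves dropout bias wholly uncorrected. Neither follows. Incomplete variables can overlap with predictors of dropout, and the mixed model already handles dropout that is missing at random given the observed outcomes.
- A reader might infer that the plan intends to condition on variables measured after randomisation. The text fails to exclude them, which is weaker.
- The harms do not simply add up. A time-varying T2 or T3 covariate would remove records at that time point, and many of those would lack the outcome anyway. A T1 covariate would cost whole participants but raises no post-randomisation problem.

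The power figures rest on assumed missing shares. They also ignore the partial responders that a mixed model keeps and the precision gained from repeated measures. At 10% the result, 0.78, is close to the planned .79.

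**Conclusion.** The sentence is wrong as written. This is a stated rule with the wrong criterion, not detail left for another document. It selects covariates by their own missingness. Taken literally, it does not help with dropout beyond the mixed model, can drop observed WHO-5 and SDQ records, and leaves T2 and T3 variables eligible.

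The documents do not support the stronger conclusion that the primary analysis will be biased or materially underpowered. That would require the literal reading, substantial missingness in the selected variables and no imputation of covariates, all together. Under those conditions, and with 1172 analysed, 25 schools per arm, intraclass correlation 0.02 and d = 0.20, power would fall from about 0.81 to 0.78, 0.75 or 0.71 at 10, 20 or 30% missing. The missing shares are assumptions, but the defect in the rule does not depend on them.

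**What to change.** Replace the covariate sentence under Planned Statistical Analysis with wording such as:

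*Baseline (T1) variables that predict non-response to WHO-5 or SDQ at T2/T3 in the attrition analysis will be included as covariates in the mixed models; no variable measured after randomisation will be used as a covariate; missing T1 covariate values will be imputed so that observed outcomes are retained.*

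This gives the attrition analysis, which is already planned, a stated role in the model. It changes a sentence in the protocol or analysis plan and needs no new data. The only downside is slightly more analysis work. The Results section reports that data collection was still under way, so at that stage the change could be made before the outcomes were analysed.

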### Randomization

This study is a cluster randomized controlled trial with intervention and waiting-list control groups. Schools will be randomly assigned to one of the groups by a statistician after baseline assessment. SPSS (IBM Corp) will be used to generate a random number between 0 and 1 that will be assigned to each school. The half of the schools with lower values for the random number will be assigned to the control group and the half of the schools with higher values will be assigned to the intervention group.

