### Outcomes

Data will be collected at 3 measurement points: baseline (T1; preintervention); approximately 2 weeks after the intervention (T2; postintervention); and approximately 1 month after the intervention (T3; follow-up) through self-report measures that the adolescents fill in using the secure online tool Nettskjema (University of Oslo).

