### Primary Outcomes

Mental health will be assessed using the World Health Organization–5 Well-being Index (WHO-5) [21] and the Strengths and Difficulties Questionnaire (SDQ) [22]. Both the WHO-5 [23] and the SDQ [24] have been found to have adequate validity as outcome measures. The primary hypothesis is that there will be significant differences in changes in the mental health scores of the intervention and the control groups in favor of the intervention group.

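### The planned test reads as a change-score comparison; because schools are randomised after baseline, constraining or adjusting for T1 would give a more precise estimate from the same data

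*Protocol article*

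**What the plan says.** Under Primary Outcomes, the protocol article hypothesises that "there will be significant differences in changes in the mental health scores of the intervention and the control groups", in favour of the intervention. Outcomes are collected at T1 (before the intervention), T2 (about 2 weeks) and T3 (about 1 month).

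Under Planned Statistical Analysis, "linear mixed models will be used to test the hypotheses". The structure is given as follows: "We will run 3-level mixed models with time nested within participants nested within schools". The covariance of the repeated measures is to be chosen by the Akaike information criterion. The only rule for covariates is that "Variables for which there are a significantly greater number of missing values will be included as covariates in the analyses". The T1 score is not named as a covariate, and no constraint on the T1 means is mentioned.

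Under Randomization, "Schools will be randomly assigned to one of the groups by a statistician after baseline assessment". Under Blinding, schools, guardians and adolescents do not know their arm before the baseline assessment.

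**The concern.** Suppose T1, T2 and T3 are all outcomes and each arm has its own T1 mean. With complete data, the group-by-time contrast is then the difference between arms in mean change from T1. That model spends information on estimating a T1 difference that randomisation after baseline has already set to zero in expectation. It also subtracts the whole of any chance T1 imbalance from the effect estimate, whereas an adjusted or constrained analysis subtracts only the part that predicts the follow-up score. With schools as the unit of randomisation, such imbalance is not trivial.

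What is at stake is precision, not validity. Precision matters here because the article itself describes app effects as generally small, and because 381 adolescents had answered the first questionnaire against a recruitment target of 1563 when it was written.

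**Working it through.** **Inputs from the article (Power Calculations):** significance level .05 (taken as two-sided), d = 0.20, ICC 0.02, 625 adolescents per arm. Since 25 × 25 = 625, this is read as 25 schools of 25 students in each arm.

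**Inputs that are assumptions:** the individual T1-to-follow-up correlation ρ, shown from 0.3 to 0.8; the autocorrelation λ of the school effect over time, shown at 1.0 (a constant school intercept) and 0.8; an outcome variance of 1 at each wave.

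**The plan's own power figure.** The design effect is 1 + 24 × 0.02 = 1.48. A comparison of follow-up means alone has power 0.828 (normal approximation) or 0.813 (t with 48 df), against the stated .79. Small unstated settings close the gap: an ICC of 0.024, which rounds to 0.02, gives 0.788, and a cluster-size coefficient of variation of 0.4 gives 0.792. The stated figure is not shown to be wrong, and it does not bear on this point.

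**Variance of the two analyses, on school means, for one follow-up time.**
- Variance of a school mean: V = 0.02 + 0.98/25 = 0.0592.
- Correlation of school means over time: r = (0.02λ + 0.0392ρ)/0.0592.
- Change score: 2V(1 − r).
- Constrained or adjusted for T1: V(1 − r²).
- Relative reduction: 1 − (1 + r)/2 = (1 − r)/2, which is never negative.

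Example with ρ = 0.5 and λ = 1.0: r = (0.0200 + 0.0196)/0.0592 = 0.669, and the reduction is 0.331/2 = 16.6%.

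| ρ | r (λ = 1.0) | reduction | r (λ = 0.8) | reduction |
|---|---|---|---|---|
| 0.3 | 0.536 | 23.2% | 0.469 | 26.6% |
| 0.4 | 0.603 | 19.9% | 0.535 | 23.2% |
| 0.5 | 0.669 | 16.6% | 0.601 | 19.9% |
| 0.6 | 0.735 | 13.2% | 0.668 | 16.6% |
| 0.7 | 0.801 | 9.9% | 0.734 | 13.3% |
| 0.8 | 0.868 | 6.6% | 0.800 | 10.0% |

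**Power at d = 0.20** (t with 48 df, variance of the arm difference = 2 × school-level variance / 25), change score against adjusted:
- ρ = 0.5: 0.938 against 0.969 (λ = 1.0), a gain of 3.1 points; 0.890 against 0.946 (λ = 0.8), a gain of 5.6 points.
- ρ = 0.7: 0.995 against 0.997 (λ = 1.0); 0.974 against 0.987 (λ = 0.8).

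**Chance imbalance at T1.** The SD of the difference between arm means at T1 is √(2 × 0.0592/25) = 0.069 outcome SD, so the 95% range is about ±1.96 × 0.069 = ±0.135. At r = 0.669, an imbalance at the edge of that range moves the change-score estimate by 0.135 × (1 − 0.669) = 0.045 SD relative to the adjusted one, or 0.045/0.20 = 22% of the target effect. Over repeated randomisations this averages to zero.

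**Change score against ignoring baseline.** The two break even at r = 0.5, that is at ρ = (0.0296 − 0.02λ)/0.0392. This is ρ = 0.245 for λ = 1.0 and ρ = 0.347 for λ = 0.8. It reaches 0.5 only if λ is as low as 0.5.

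**The case against.** The strongest reply is that the criticised model is not written down. The article gives the levels, the software command and the way the covariance will be chosen, but no fixed effects. A difference in changes also fits the remedy: if both arms share the T1 mean, the arm difference at T3 is the difference in change. The exact specification may sit in an analysis plan that is not shown. This stands in part, and the point is therefore conditional on the natural reading. That reading is still well founded: the article fixes the form of the hypothesis, puts T1 among the repeated measures and names a covariate rule that leaves out T1.

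A second reply is that a group-by-time mixed model over all waves is a legitimate analysis of a randomised trial. That stands in full. A reader might infer that the plan is biased or invalid; the documents do not support this.

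A third reply concerns size. A reader might apply the participant-level formula (1 − ρ)/2 and expect 15% to 25% for correlations of 0.5 to 0.7. No correlation is given in the article, and that formula ignores the randomisation by school. With the article's clustering, the same correlations give about 10% to 17% (constant school effect) or 13% to 20% (school autocorrelation 0.8). Likewise, a reader might infer that a correlation below 0.5 makes the change analysis worse than ignoring baseline. As a general statement this fails: with a constant school effect the break-even correlation is about 0.25.

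Finally, the remedy is not literally free. A school-mean covariate uses a between-school degree of freedom, and the constrained and covariate models treat a missing T1 score differently.

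**Conclusion.** The point holds as a recommendation on efficiency. On the natural reading, the plan tests a change-score contrast although randomisation after baseline allows a more precise analysis, one that is asymptotically never worse. The variance of the treatment contrast would fall by (1 − r)/2: about 7% to 27% over assumed individual correlations of 0.3 to 0.8, and about 10% to 20% for 0.5 to 0.7. At d = 0.20 and a correlation of 0.5 this is worth roughly 3 to 6 points of power.

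These figures rest on assumed correlations, a school autocorrelation of 0.8 to 1.0, equal variances over time, 25 schools of 25 students per arm, and a contrast at a single follow-up. In the ρ = 0.5 and ρ = 0.7 cases shown, the change analysis already exceeds the stated .79 with the full sample, so the gain improves the design and does not rescue it.

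**What to change.** State in the analysis section how T1 enters the model, in one of two ways:
- Keep T1, T2 and T3 as outcomes but omit the group main effect, so that both arms share the T1 mean and the treatment effects are the arm differences at T2 and T3 (constrained longitudinal analysis).
- Model T2 and T3 only, with the individual T1 score and the school-mean T1 score as covariates.

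The random effect for school and the choice of covariance structure can stay as planned. If the covariate version is chosen, say how missing T1 scores are handled. The cost is negligible: one part of the model specification and, for the covariate version, one between-school degree of freedom (47 instead of 48 with 25 schools per arm). No new data are needed. The choice should be recorded before the outcome data are analysed by arm.

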### Ethics Approval and Consent to Participate

The study, including the information letter sent to the guardians and study participants and the consent forms, has been approved by the regional Research Ethics Committee (279207) and by the Norwegian Center for Research Data (715456). The study has been registered on ClinicalTrials.gov (NCT05211713). Active parental consent from 2 guardians is required for adolescents that are younger than 16 years to participate in the effectiveness study. Adolescents that are aged 16 years or older can consent by themselves. Consent, as well as the answers adolescents provide, will be collected digitally using Nettskjema and stored using the services for sensitive data of the University of Oslo in Norway [31]. It is possible that there will be unintended adverse effects of using the app or answering the survey that adolescents might find distressing [18]. Therefore, we will provide information about where the adolescents can receive help if they need it in the app, in the information letter, and at the end of the survey. Participants that fill in the 3 questionnaires will be entered in a raffle for 1 of 100 gift cards with a value of NOK 300 (approximately US $29). The app itself does not collect personal or sensitive information about the users, nor does it need access to GPS, the camera, contact lists, or anything else on the mobile phone.

## Results

Recruitment and data collection started in August and September 2022. However, teachers were on strike at that point for about 6 weeks, which made recruitment challenging as the schools were partly closed. Data collection was expected to end in December 2022 but had to be prolonged until approximately June 2023. So far, 381 adolescents have answered the first questionnaire. The results of the study will be available at the earliest at the end of 2023 or later, and will be published in international and national journals and presented at conferences.

## Discussion

### Principal Aims

The current paper describes a cluster randomized controlled trial that is being conducted to evaluate the effectiveness of a universal mental health–promoting mobile app (Opp) in Norway. Its evaluation will lead to new knowledge in the field, as there have been only a few studies published on the effectiveness of such universal interventions [15]. Fusar-Poli et al [2] wrote that “Promotion of good mental health in young people with and without mental disorders has received little empirical research attention and interventions for improving mental health in young people are not well established.” Conducting well-designed effectiveness studies is challenging. However, they are necessary in order to identify interventions effective at improving child and adolescent mental health. Randomized controlled trials are considered the gold standard for evaluating the effectiveness of interventions [18].

After the effectiveness study is conducted, Opp will be made freely available in the Google Play and App Store. Results of the study will continue to be published as they are obtained.

### Limitations

Several limitations will have to be considered when interpreting the results. Both the adolescents and schools are convenience samples, which could lead to selection bias and limit the conclusions that can be drawn from the study [32]. Another limitation is related to the randomization, which will be conducted on a school level and not an individual level [33].

Other limiting factors are related to adherence to the intervention and intervention fidelity. The app does not collect personal data from its users, and it is therefore not possible to objectively track if and how often the adolescents have used the app. However, the intervention group will answer app-related questions on the frequency of use. Both the intervention and control groups receive the same information letter, and participants that are randomized to the intervention group are informed that they can use the app whenever they want and as often as they want, without further instructions. In addition, the intervention group receives a text message with a code to unlock the app after the baseline assessment and randomization.

Another limitation is related to the length of follow-up, which should ideally be longer than 1 month. Kenny et al [15] wrote the following regarding this: “Findings suggest that a 4-week app-based intervention may not be enough to elicit intrapersonal changes in mental health outcomes in a general adolescent population.” Furthermore, the study is based on self-report measures and not on more objective indicators or assessments from other informants, such as parents or teachers, which might be a limitation.

